#### WP5: pilot implementation and evaluation of implementation package

The implementation strategy for the interventions will be co-designed with the stakeholders and nested into the existing public health services in each selected district. We will implement the strategies through a single-arm trial in four randomly chosen blocks in each district. Data will be captured during pre-intervention, intervention and post-intervention period. Data collected from the initiation of interventions will show whether any baseline secular trends have changed in the blocks (before and after intervention).

In addition, the costing protocol will be tested during pilot implementation of the intervention strategies and adapted as needed to the existing public health infrastructure. The adaptation will produce a custom costing tool for on-going use in each district that will support local officials for budgeting purposes.

We will define and measure outputs (direct products of activities and will include types, levels and targets of services to be delivered) and SMART outcome indicators such as specific changes in health-seeking behaviour, changes in health providers’ knowledge and skills, adoption of acquired skills, access and participation to cancer early detection and treatment and diagnostic intervals in the selected blocks. Similar indicators measured in the pre-intervention period will allow us to correlate between the interventions and their impact. Most of these outcomes will be implementation outcomes, though we will measure effectiveness outcomes such as interval between symptom onset and diagnosis confirmation or interval between screening and further assessment/treatment, detection and stage of precancers and cancers and so on.

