#### Tamil Nadu

This southern state of India has a proportion of 4.89% of multidimensional poor, ranking 4th lowest [17]. The state has a well-organized health system and ranks third on the national SDG Index with a score of 67. It also has the longest running cancer screening program in India. Crude incidence and age-standardized cancer incidence rates in Tamil Nadu are 96.1 and 86.4 per 100,000, respectively. This present study is planned at the Viluppuram district (population according to Census 2011: 3,458,873) of Tamil Nadu, which has a predominantly rural population (86%) and a high cancer burden. It has nine taluks (Viluppuram, Vikkiravandi, Vanur, Kandachipuram, Thiruvennainallur, Tindivanam, Gingee, Melmalaiyanur and Marakkanam). The Tamil Nadu Cancer Registry Project in 2016 reported cervical cancer followed by breast cancer to be the most common cancer among women in the Viluppuram district. Oral cancer was the third most common cancer among both males and females. The population coverage of the state-run screening program is low and an organized screening program undertaken by the Cancer Institute (WIA) is in progress. Tamil Nadu has an ongoing government-run facility-based opportunistic cancer screening program for cervical and breast cancer since 2012 and an oral cancer screening program since 2017. Apart from this, an organized community-based cancer screening program has been conducted by the participating institution since 2015 [24, 25].

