#### WP2: assessing barriers and facilitators in implementing a CHW-led early detection strategy and treatment services for oral, breast and cervical cancers

This WP focuses on understanding the context-specific barriers, challenges and opportunities that exist for rural men and women to access the cancer early detection care continuum through a mixed-method approach. This WP encompasses the entire pathway of early detection – community mobilization for screening, access to screening and diagnostic services and navigating the systems to initiate treatment. The contextual factors at individual, provider and systems levels will be examined using the rapid assessment and response evaluation (RARE) methodology, which is a rapid ethnographic assessment to elicit beliefs and perceptions around health prevention and treatment, including assessing barriers [30]. The following components of the RARE technique will be used to study the knowledge, attitude, perceptions and beliefs of the target population: a) key informant interview (KII); b) focus group discussions (FGDs) and c) questionnaire survey. At each study site, we will identify blocks where the pilot intervention will be implemented (discussed later). The contextual factors and barrier assessment study will be implemented in these blocks.

The assessment will involve the following tasks at each study site.

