## Supplementary Table

**Supplementary file 1. table1:** Activities timeline.

Tasks	Year 1	Year 2	Year 3	Year 4
**WP1: Creating and engaging a stakeholder’s team**	**X**			
1.1 Formation of the stakeholder’s teams (independent at each site)	X			
1.2 Yearly meetings of the research team	X	X	X	
**WP2: Contextual factors assessment**	**X**			
2.1 Finalization of protocol and data collection tools	X			
2.2 Approval from ethics committees	X			
2.3 Completion of surveys, FGDs and KIIs	X	X		
2.4 Analysis of data and report finalization	X	X		
**WP3: Assessment of capacity of the local health systems**		**X**		
3.1 Finalizing the capacity assessment plan	X			
3.2 Data collection for landscape survey completed	X			
3.3 Facility visits completed	X	X		
3.4 Capacity development response finalized	X	X		
**WP4: Designing and costing a multilevel intervention strategy**		**X**		
4.1 Submission of the WP2 and WP3 outcomes to the stakeholder’s team meeting	X			
4.2 Finalization of protocol for pilot study		X	X	
4.3 Finalization of the logic model for evaluation of pilot		X	X	
4.4 Finalization of tools, databases etc. for the pilot		X	X	
4.5 Approval of ethics committees		X	X	
**WP5: Pilot implementation and evaluation of the intervention strategies**			**X**	
5.1 Initiation of baseline data capturing in intervention and control blocks		X		
5.2 Initiation of pilot interventions in intervention block			X	
5.3 Completion of data capturing of control block			X	X
5.4 Completion of the pilot interventions			X	X
5.5 Completion of data analysis of control and pilot			X	X
5.6 Finalization of the costing tool				X
**WP6: Assessment of the setting’s readiness and capacity to sustain and scale up the interventions**				**X**
6.1 Adaptation of the scalability assessment tools				X
6.2 Protocol finalized for scalability assessment				X
6.3 Completion of scalability assessment				X
**Final analysis of data and publication of results**				X

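### WP5 is described as a single-arm before/after trial, but the activities timeline schedules control-block data and their analysis; the two designs must be reconciled before baseline capture

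*Protocol article*

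**What the plan says.** The WP5 section sets the design in one sentence: "We will implement the strategies through a single-arm trial in four randomly chosen blocks in each district". Data are to be gathered before, during and after the intervention. Two sentences say how they will be used: "Data collected from the initiation of interventions will show whether any baseline secular trends have changed in the blocks (before and after intervention", and "Similar indicators measured in the pre-intervention period will allow us to correlate between the interventions and their impact". The section names no comparison blocks.

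Supplementary file 1, which the Study design section cites as the detailed study timeline, lists these WP5 tasks:

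- "5.1 Initiation of baseline data capturing in intervention and control blocks" (Year 2)
- "5.3 Completion of data capturing of control block" (Years 3 and 4)
- "5.5 Completion of data analysis of control and pilot" (Years 3 and 4)

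The Objective section includes an assessment of effectiveness, alongside implementation outcomes such as adoption and fidelity. WP5 lists effectiveness outcomes: diagnostic and treatment intervals, detection, and stage. WP6 then uses evidence of effectiveness as one of its scalability domains.

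**The concern.** The article commits to one arm in the text and to two in the timeline. The conflict covers the start, the end and the analysis of control data, so it is not a single slip of wording.

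The choice decides what the effectiveness outcomes can show. With only the pilot blocks, a change between Year 2 and Year 4 combines the strategy with whatever else changed in those districts. The article describes such activity. In Viluppuram "an organized screening program undertaken by the Cancer Institute (WIA) is in progress". The Discussion says that Kerala is setting up its Cancer Care Grid and refers to two national programmes, NPCDCS and Ayushman Bharat. The WP5 result feeds the scalability assessment and a possible extension to other states, so the strength of the causal claim has consequences.

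Timing makes this pressing. Baseline capture is due in Year 2 and the pilot starts in Year 3. A control baseline that is not collected before the pilot cannot be recovered afterwards.

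**Working it through.** **1. The two descriptions side by side.**

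| Feature | WP5 section | Supplementary file 1 |
|---|---|---|
| Arms | One | Intervention and control |
| Baseline data | Pilot blocks | Intervention and control blocks (5.1) |
| Follow-up data | Pilot blocks | Control-block capture completed (5.3) |
| Analysis | Before against after, change in trend | Control and pilot (5.5) |
| Number of control blocks | None | Not stated (plural in 5.1, singular in 5.3) |

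The timeline is current text, cited in the body, and not a log of superseded wording. No reading makes both columns true. Drawing the pilot blocks at random does not resolve this: it makes them representative of their district but does not allocate blocks between a strategy and a comparator.

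**2. What a single-arm series can and cannot separate.** Write the observed change in the pilot blocks as

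change = strategy effect + continuing prior trend + effect of concurrent new events.

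- The prior trend can be estimated and subtracted if there are enough pre-intervention time points. The article fixes no number of time points, and baseline capture begins only the year before the pilot.
- A new concurrent event falls in the same period as the strategy, so a single series cannot split the second source from the first.
- With control blocks, change(intervention) − change(control) removes whatever is common to both, provided that the strategy does not reach the control blocks.

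**3. Which concurrent events matter.** According to the Tamil Nadu section, the state programmes date from 2012 and 2017 and the organised community programme from 2015. Their existing level and trend are therefore already in the baseline, and only an intensification would confound. The Rajasthan section reports no screening activity. The Kerala grid, described as currently being established, is the clearest new change.

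**4. Size.** WP5 states no sample size, power or significance level, so there is no WP5 figure to reproduce. The following is an illustration only. All of its inputs are assumptions, except that n is borrowed from the WP2 survey: 480 × (1 − 0.20) = 384 respondents per state.

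Assume 384 people before and 384 after, a baseline indicator p0 = 30%, no strategy effect, background drift δ, a two-sided 5% test and independent samples. Then, with p1 = p0 + δ,

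P(significant rise) ≈ Φ( δ / √{[p0(1−p0) + p1(1−p1)]/n} − 1.96 ).

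- δ = 5 points: 0.05/√(0.4375/384) = 1.481; Φ(−0.479) = 0.316.
- δ = 10 points: 0.10/√(0.4500/384) = 2.921; Φ(0.961) = 0.832.
- With an assumed design effect of 2 (effective n = 192): 1.047 and 2.066, giving about 0.18 and 0.54.

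No section plans to repeat that survey after the pilot, so these numbers show the mechanism and are not error rates of this trial.

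**The case against.** The strongest case for the article is that implementation outcomes come first. WP5 says that most of its outcomes are of that kind, and the Discussion defends the hybrid design on pragmatic and political grounds. Implementation outcomes tolerate a single arm. The article also says that a pilot protocol and logic model will be developed once the strategies are chosen (tasks 4.2 and 4.3, Years 2 and 3), that separate ethical approval will be sought, and that sample size depends on the strategies. Analysis detail may properly wait for those documents. This stands as far as it goes, but it does not explain why the article already commits to both designs.

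Three stronger readings are tempting, and the documents do not support them.

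- *A single-arm design could attribute nothing.* The article's stated question is whether secular trends change, not a bare before/after difference. A suitable time series could deal partly with a stable trend. The limit is narrower: no time points are fixed, and concurrent events remain inseparable.
- *The contrast could be picked after the data are seen.* That would require knowing that the pilot protocol will set no rule, and it is still to be written.
- *Control blocks would have no baseline.* WP2 is indeed confined to the pilot blocks ("The contextual factors and barrier assessment study will be implemented in these blocks"), but WP2 is a barrier assessment, and task 5.1 separately schedules baseline capture in control blocks.

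Controls also have drawbacks. Referral guidelines, helplines and designated facility nurses may operate across block boundaries, and strategies may differ between districts.

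**Conclusion.** The contradiction holds on the text alone and needs no assumption: the WP5 section has one arm and the timeline has a control group. It should be resolved before baseline capture starts.

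The consequence is conditional. If the trial is single-arm, change in the pilot blocks is weak evidence that the strategy improved early detection, because new or intensified state and national activity cannot be separated from it. If control blocks are kept, the effectiveness outcomes can rest on a controlled comparison, subject to contamination.

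The size of any bias cannot be derived from the article. A reader might take 32% and 83% as the false-positive risk of this trial. They are not: they assume a repeat survey that nobody has planned, a 30% baseline, chosen drifts and no clustering, and they fall to about 18% and 54% under an assumed design effect of 2. The importance of the point rests on the conflicting designs and the effectiveness aim, not on these figures.

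**What to change.** Choose one design and make the WP5 section and Supplementary file 1 agree.

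**(a) Control blocks kept.** Replace the single-arm label in WP5. State how many control blocks there are per district and how they are selected, preferably by random allocation of listed blocks within district. Collect the same baseline and follow-up indicators in both groups. Base the effectiveness outcomes on the difference in change between intervention and control blocks, reported by district because strategies may differ. State how contamination from strategies that cross block boundaries will be recognised.

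Control-block data capture is already in the activity plan, so most of the cost is wording. It is not free if the WP2 survey is also spread over control blocks. For example, dividing the 384 expected respondents per state equally gives 192 per arm. At 50% prevalence and ignoring clustering, the 95% half-width rises from 1.96 × √(0.25/384) = 5.0 points to 1.96 × √(0.25/192) = 7.1 points per arm.

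**(b) Control blocks dropped.** Remove them from tasks 5.1, 5.3 and 5.5. Report the WP5 effectiveness outcomes as within-block change, without causal attribution to the strategy. This costs only wording, and a weaker claim is carried into WP6.

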#### WP6: assessment of setting’s readiness and capacity to sustain and scale up interventions

We will use the validated Intervention Scalability Assessment Tool (ISAT), which is designed to assist practitioners, policymakers, programme managers and researchers to determine the scalability of a discrete health programme or intervention [33]. The tool consists of three sections and each section has multiple domains.

Part A: It consists of five domains: 1) the problem; 2) the intervention; 3) strategic and political context; 4) evidence of effectiveness and 5) intervention costs and benefits.Part B: It consists of five domains: 1) fidelity and adaptation; 2) reach and acceptability; 3) delivery setting and workforce; 4) implementation infrastructure and 5) sustainability.Part C: It summarizes all the information gathered to facilitate the process of making a recommendation on scalability.

### Sampling methodology and sample size estimation

WP2 involves a population survey. A multistage cluster sampling design will be employed to select participants for the surveys. Blocks will serve as the primary sampling units and households as the secondary sampling units. Based on an expected 50% prevalence of knowledge and understanding about common cancer symptoms and assuming a 10% precision, 95% confidence level and 20% nonresponse rate, a total sample size of 480 is estimated for each state [36]. This sample size will be proportionally divided among randomly selected blocks. Subsequently, the number of households from each block will be proportionately distributed using systematic sampling from a list of households. One respondent from each household, alternating male and female, will be chosen to get equal male and female participants. The number of participants required for the hospital-based survey in WP2 has been empirically decided at 100 patients with breast, cervical and oral cancer from each study site. It is estimated that a minimum of six FGDs per state will be conducted or more until saturation is achieved.

For WP3, the services will be broadly categorised into primary, secondary and tertiary healthcare settings. The number of facilities to be sampled will be calculated using the standard formula for a proportion using an expected percentage of health facilities offering a given service as the outcome. An expected proportion of 90% of service availability will be used, with 95% confidence within an error margin of 20%, assuming a nonresponse rate of 10% of the selected facilities. If the total number of a particular type of facility for each stratum is small (<4) in the district, all facilities may be included.

For WP4, the sample size will depend on the interventions and strategies selected to be piloted and evaluated.

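### The WP2 survey size of 480 per state is a simple-random-sampling figure, so its stated precision is overstated for the declared cluster sample of blocks

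*Protocol article*

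**What the plan says.** All of this is in the protocol article. Under Sampling methodology and sample size estimation, the design is stated first: "A multistage cluster sampling design will be employed to select participants for the surveys". The stages follow: "Blocks will serve as the primary sampling units and households as the secondary sampling units". The inputs come next: "Based on an expected 50% prevalence of knowledge and understanding about common cancer symptoms", "assuming a 10% precision, 95% confidence level and 20% nonresponse rate", and from these "a total sample size of 480 is estimated for each state". The article does not say whether the 10% is relative to the 50% or absolute in percentage points. It lists no design effect, ICC or number of survey blocks among the inputs.

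The number of blocks follows from two other sections. WP2 says of the blocks chosen for the pilot: "The contextual factors and barrier assessment study will be implemented in these blocks". WP5 sets the pilot in "four randomly chosen blocks in each district". Under Study setting, Kerala and Tamil Nadu contribute one district each and Rajasthan two. WP4, however, speaks of three target districts, so Rajasthan may have four blocks or eight.

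**The concern.** The section names a cluster sample but supports its size with a precision statement that fits an unclustered one. Residents of the same block share health facilities, community health workers and past screening campaigns, so their answers on cancer knowledge and access are likely to be correlated. With about 96 responders per block, even a small correlation matters.

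The WP2 findings go to the stakeholder workshop that chooses the intervention package in WP4. If readers there take 480 per state to deliver ±5 points, differences between states, or distances from a target, will look firmer than the design can support. No hypothesis test in the article rests on this figure, so what is at stake is how the formative results are read.

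**Working it through.** **Inputs.** From the sampling section: p = 0.50, 95% confidence (z = 1.96), 10% precision, 20% nonresponse, stated size 480 per state. From WP2, WP5 and Study setting: four blocks in Kerala and in Tamil Nadu; eight in Rajasthan if both districts count. The article also says "One respondent from each household, alternating male and female, will be chosen to get equal male and female participants", so there is no clustering of respondents within households and the block is the level that matters. The ICC is assumed at 0.01 to 0.05.

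**Step 1: reproduce 480.** n = z² × p(1 − p) / d², then divide by (1 − 0.20).

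- Relative reading, d = 0.10 × 0.50 = 0.05: 1.96² × 0.25 / 0.05² = 384.16, and 384.16 / 0.8 = 480.2. This matches 480 with a design effect of 1.
- Absolute reading, d = 0.10: 1.96² × 0.25 / 0.10² = 96.04, and 96.04 / 0.8 = 120. To reach 480 this needs an unstated factor of 480 / 120 = 4.

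**Step 2: precision under the declared design.** Responders: 480 × 0.8 = 384. Design effect = 1 + (m − 1) × ICC, with m = 384 / 4 = 96 or 384 / 8 = 48. Half-width = critical value × √(0.25 × design effect / 384). The critical value is 1.96, or t on 3 df = 3.182 for four blocks.

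| Assumed ICC | Four blocks: design effect | Effective n | Half-width, z | Half-width, t (3 df) | Eight blocks: design effect | Half-width, z |
|---|---|---|---|---|---|---|
| 0.01 | 1.95 | 197 | 7.0 | 11.3 | 1.47 | 6.1 |
| 0.02 | 2.90 | 132 | 8.5 | 13.8 | 1.94 | 7.0 |
| 0.05 | 5.75 | 67 | 12.0 | 19.5 | 3.35 | 9.2 |

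Half-widths are in percentage points. Under simple random sampling the value is 1.96 × √(0.25 / 384) = 5.0.

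**Step 3: can more households repair it?** As m grows, the half-width falls no lower than 1.96 × √(0.25 × ICC / number of blocks). With four blocks and an ICC of 0.02 this is 1.96 × √(0.25 × 0.02 / 4) = 6.9 points. The ±5 points is then out of reach however many households are added.

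**Step 4: the absolute reading.** The factor of 4 is used up when 1 + 95 × ICC = 4, that is at ICC = 3 / 95 = 0.032 with z. With t on 3 df the allowable design effect is (0.10 / 3.182)² × 384 / 0.25 = 1.52, so the limit is 0.52 / 95, about 0.005.

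**Simplifications.** Blocks are taken as equal in size. No finite-population correction is made for the share of a district's blocks that is sampled, because the article does not give the number of blocks per district. Such a correction would narrow the half-widths for district-level inference.

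**The case against.** The best defence is that no state-level inference is intended. The sites were chosen purposively, Kerala and Tamil Nadu contribute one district each, and WP2 is meant to describe barriers where the pilot will run. On that view 480 is an allocation per site, the selected blocks are the whole target, they act as strata, and no block-level design effect is needed. This is a coherent plan, and under it about ±5 points stands. It is not the plan as written, though: the sampling section calls the blocks primary sampling units, selects them at random and attaches the precision to each state. Purposive choice of district also means that block-level standard errors support inference to the district at most.

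A second defence is the absolute reading of 10%, under which 480 leaves room for a design effect of 4. With z, ±10 points is then met at ICC 0.01 and 0.02. That also stands, but the article mentions no such factor, and with only four blocks the t-based margin is much thinner.

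Third, every ICC here is assumed. That is true. On the relative reading, however, 480 has no slack, so before any finite-population correction any positive ICC takes the half-width above 5 points. The ICC decides only by how much.

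A reader might go further and infer that the reported confidence intervals will be too narrow. The article does not support this. Data analysis gives no estimation method for the household survey, and leaving a design effect out of planning makes a correct interval wider than planned. It would be too narrow only if the analysis ignored clustering.

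**Conclusion.** The precision behind 480 is overstated for inference beyond the selected blocks, on the reading of 10% that reproduces the figure. With four blocks the expected half-width is 7.0 to 12.0 points with z, or 11.3 to 19.5 with t on 3 df, against 5.0. With eight blocks it is 6.1 to 9.2 with z. These figures rest on an assumed ICC of 0.01 to 0.05, 384 responders and equal blocks. If 10% is absolute, the fault is smaller: an unexplained factor of 4 that covers clustering with z up to an ICC of about 0.03.

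Two further inferences are tempting and are not supported. One is that taking one adult per household tilts estimates towards small households. That needs both an unweighted analysis and knowledge that varies with the number of eligible adults; the documents state neither, and weighting and respondent selection are commonly left to an analysis plan or to the operating procedures promised under Study monitoring. The other is that this survey is the WP5 baseline. The activities timeline lists WP5 baseline data capture as a separate task in Year 2.

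**What to change.** Keep 480 per state. State whether the 10% is relative or absolute, and how many blocks the survey uses in each state. Then choose one of two routes:

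1. Keep blocks as primary sampling units. Restate the expected precision under the cluster design over an ICC range of 0.01 to 0.05, and analyse with design-based standard errors at block level.
2. Declare the selected blocks as strata, limit inference to them, and drop the precision claimed per state.

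Either route is a change of wording and analysis and needs no extra fieldwork. The first costs a visibly wider stated precision; the second costs a narrower target population.

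### The WP2 survey size of 480 per state needs the 10% precision to be relative, which is not stated, and then makes no allowance for the cluster design

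*Protocol article*

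**What the plan says.** The calculation is in the Protocol article, section Sampling methodology and sample size estimation. The starting point is "Based on an expected 50% prevalence of knowledge and understanding about common cancer symptoms", followed by "assuming a 10% precision, 95% confidence level and 20% nonresponse rate, a total sample size of 480 is estimated for each state". A literature reference is attached to the figure.

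The same paragraph sets out the sampling: "A multistage cluster sampling design will be employed to select participants for the surveys". It adds: "Blocks will serve as the primary sampling units and households as the secondary sampling units". The 480 are shared proportionally among randomly selected blocks. Households are then drawn systematically from lists, with one respondent per household and men and women alternating.

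Two other sections bear on the number of blocks. The WP2 section places the barrier assessment in the blocks where the pilot will run. The WP5 section puts the pilot in four randomly chosen blocks per district.

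**The concern.** Two things are unclear in a calculation that otherwise looks complete.

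First, 10% precision around a 50% prevalence can mean ±10 percentage points, or 10% of 50%, which is ±5 points. The two readings differ fourfold in sample size, and only one reaches 480 without a further factor.

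Second, on the reading that does reach 480, the four stated inputs use up the whole figure. Nothing is left for clustering, although blocks are named as the primary sampling units.

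At stake is the precision with which each state's survey estimates will be read. Someone who takes ±5 points from the calculation will treat the estimates as more exact than a block-clustered sample allows. Someone who takes ±10 points cannot see how 480 was obtained.

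**Working it through.** **Inputs** (all from Sampling methodology and sample size estimation): p = 0.50; precision 10%, type not stated; 95% confidence, so z = 1.96; nonresponse 20%; stated result 480 per state.

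**Formula:** n = z² p(1 − p)/d² completed interviews, then N = n/(1 − 0.20).

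**Step 1: reproduce 480.** With relative precision, d = 0.10 × 0.50 = 0.05.
- n = 1.96² × 0.25/0.05² = 384
- N = 384/0.80 = 480, which matches.

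**Step 2: the other reading.** With absolute precision, d = 0.10.
- n = 1.96² × 0.25/0.10² = 96
- N = 96/0.80 = 120
- Reaching 480 would need a further factor of 480/120 = 4, and none is stated.

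Inflating by 1.2 instead of dividing by 0.8 gives about 461 (relative) or 115 (absolute). Neither matches.

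**Step 3: what design effect does Step 1 contain?** 384/0.80 already equals 480, so the implied design effect is 1.

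**Step 4: precision of 384 completed interviews under clustering.** Half-width = 1.96 × √(0.25 × deff/384). The documents give no design effect, so these values are assumptions.

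| Assumed deff | Half-width (points) | N per state to hold ±5 points |
|---|---|---|
| 1.0 | ±5.0 | 480 |
| 1.5 | ±6.1 | 721 |
| 2.0 | ±7.1 | 961 |

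The last column is 384.16 × deff/0.80, rounded up for the two clustered rows.

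**Step 5: the block structure.** Kerala and Tamil Nadu have one study district each. If the survey uses that district's four pilot blocks, there are about 384/4 = 96 respondents per block. Then deff = 1 + (96 − 1) × ICC. The ICC values are assumed.

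| Assumed ICC | deff | Half-width (points) |
|---|---|---|
| 0.01 | 1.95 | ±7.0 |
| 0.02 | 2.90 | ±8.5 |
| 0.05 | 5.75 | ±12.0 |

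Rajasthan has two study districts. Eight blocks would mean about 48 respondents per block and smaller losses: deff = 1 + 47 × ICC = 1.47, 1.94 and 3.35, or about ±6.1, ±7.0 and ±9.2 points.

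**The case against.** The strongest reply is that the arithmetic is sound. Relative precision is a standard convention, it uses every stated input, and it returns 480 exactly. This stands. A reader might infer from the 120 in Step 2 that 480 is an arithmetic error or fourfold too large. The documents do not support that, because the gap exists only if the 10% is taken as percentage points, which the text does not say.

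A second reply is that a hidden factor of 4, such as a design effect of 2 applied to each of two sexes, is speculation. This also stands in part. The text gives one total per state and sets no precision target by sex, so the factor is not needed to explain 480, though it cannot be excluded. For the same reason, wider intervals for men and women separately are not a defect in the plan.

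A third reply is that the article condenses a fuller protocol and cites a source that is not at hand, so the design effect may be dealt with elsewhere. This carries less weight. The article prints a full set of inputs and a result, and on the reading that links them there is no room for a design effect.

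Finally, if the blocks were treated as fixed strata, the loss would be smaller than in Step 5. But the text says they are randomly selected and calls them primary sampling units.

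**Conclusion.** The point holds in a limited form. The 480 follows from the stated inputs only if the 10% is relative, which the text should say. On that reading it is a simple-random-sample size for a survey described as multistage cluster sampled, and ±5 points is not achieved if responses are correlated within blocks. The alternative, ±10 points absolute, needs an undeclared factor of 4.

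The size of the loss depends on assumptions: about ±6 to ±7 points at design effects of 1.5 to 2.0, and ±7 to ±12 points with four blocks of 96 and an ICC of 0.01 to 0.05. The four-block case also assumes that the survey is confined to the pilot blocks of a one-district state.

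Severity is moderate. A reader might go further and treat this survey as the baseline for judging the pilot, or as the study's largest data collection. The documents do not establish either. WP2 is there to inform the co-design, the activities timeline lists baseline capture separately under WP5, and the sample size for piloting is left open.

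**What to change.** Keep 480 per state and restate its basis:
- Say that the 10% is relative to the expected 50%, so ±5 percentage points, from 384 completed interviews before any allowance for clustering.
- Give the number of blocks per state, an explicit design effect (or an assumed ICC and block size) with its source, and the precision expected after it.
- If ±10 points absolute was intended, say so and state the design effect or other multiplier, 4 in total, that takes 120 to 480.

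The cost is a sentence or two, with no change in enrolment. The drawback is that the stated precision becomes less favourable. If the investigators want to hold ±5 points after clustering, the sample would have to grow, to about 721 per state at an assumed design effect of 1.5 or 961 at 2.0. Restating the precision avoids that.
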